### 5.1.1 Cohort Progression Guidelines

For Part 1 (SAD), the decision to proceed to subsequent dosing cohorts will be made by the

Sponsor in consultation with the PI based on a blinded review of the emerging safety data and PK data, if available. Three additional dose cohorts may be enrolled at the discretion of the Principal Investigator (PI) and Sponsor based on the emerging PK profile and the presence of an acceptable safety profile. The dose(s) to be administered and the form of administration (tablet or oral suspension) will be determined by the sponsor. The planned dose escalation schema may be amended based on the emerging PK and safety data. However, the maximum dose administered will not exceed 1500 mg or the maximum mean plasma exposures that were obtained for ALS-022227 in toxicology studies conducted in the dog (i.e., an  $AUC_{0-24} > 75500$  ng·h/mL). In addition, there will be no more than a three-fold increase in dose per cohort. For the 3rd and subsequent cohorts, dose escalation cannot proceed without review of the PK data from two dose levels below the next cohort.

For Part 3 (MAD), the decision to proceed to subsequent dosing cohorts will be made by the Sponsor in consultation with the PI based on a blinded review of clinical safety data through Day 9. In addition, during Part 3, representatives of the Sponsor who will have no direct involvement in the day to day activities of the study will review the HCV RNA data to confirm the dose to be evaluated for the next cohort. Subsequent dose levels may be amended on the basis of the emerging safety, PK and/or HCV RNA data. In the presence of an acceptable safety profile, the dose to be evaluated in the next cohort may be increased if the data suggest that improvements in either PK or HCV RNA concentrations are still possible. Alternatively, the dose to be evaluated in the next cohort may be decreased if the data suggest that there is value in exploring a lower intermediary dose. However, the highest dose level evaluated will not exceed the maximum tolerated dose in Part 1 or the maximum mean plasma exposures that were obtained for ALS-022227 in toxicology studies conducted in the dog (i.e., an  $AUC_{0-24} > 75500$  ng·h/mL). In addition, there will be no more than a three-fold increase in dose per cohort.

All 8 healthy volunteers or 8 of the 10 subjects with CHC in each cohort must complete the dosing schedule before a decision is made to proceed to subsequent dosing cohorts. Additional subjects may be recruited to evaluate a dose further if the data obtained from the initial cohort is not sufficiently robust for any given dose level. A decision to replace subjects for reasons other than safety-related will be made by the Sponsor in consultation with the PI.

Dose escalation will be suspended:

- If 4 or more subjects in a dose cohort experience moderate AEs or toxicities considered possibly or probably related to study drug, OR
- If 2 or more subjects in a dose cohort experience severe AEs or toxicities considered possibly or probably related to study drug, OR

- If one or more subjects in a dose cohort experience life threatening AEs or toxicities considered possibly or probably related to study drug. In this case, the Sponsor's Medical Monitor will review the treatment allocation to determine if the subject is receiving study medication or placebo. If the subject was receiving placebo then dose escalation may recommence, OR
- If 3 or more subjects in a dose cohort experience a sustained QTcF greater than 500 msec associated with an increase greater than 60 msec , OR
- If 3 or more subjects in a dose cohort experience a sustained resting heart rate of greater than 100 beats per minute

If dose escalation is suspended, a more comprehensive review of the safety data will be undertaken by the Sponsor and the PI. Based on this review, a decision will be made to continue with dose escalation, repeat a previously evaluated dose, evaluate a lower dose, modify the protocol, or terminate the study.

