## **2.0 STUDY DESIGN**

### **2.1 SUMMARY**

This randomized, double-blind, placebo-controlled, 3-part study will assess the safety, tolerability, and pharmacokinetics of orally administered AL-335 in healthy volunteers (HV) and subjects with CHC infection.

Part 1: HV will receive one of 5 single ascending doses (SAD) of AL-335 ranging from 100 mg to 1200 mg. Within each cohort subjects will be randomized to receive either AL-335 or placebo (n=8 per cohort; 6 assigned to AL-335 and 2 assigned to placebo), in a fasted state. Up to three additional cohorts may be evaluated at the discretion of the Sponsor and

Principal Investigator (PI) based on the emerging PK profile and the presence of an acceptable safety profile as outlined in Section 5.1.1. The additional cohorts may be administered an oral suspension or tablet formulation of AL-335 corresponding to one or more of the planned dose levels or to evaluate a higher dose. These doses will be evaluated under fed conditions.

Part 2: Eight HV from Cohort 3 in Part 1 will receive a second single dose of AL-335 or placebo (with a washout period of 11 to 21 days) to assess food effects on pharmacokinetics.

Part 3: The following cohorts of 10 subjects with CHC infection will be evaluated.

Subjects with CHC genotype 1 infection will receive one of 3 ascending doses of AL-335 (400 mg, 600 mg, or 800 mg) or placebo dosed once daily for 7 days (n=10 per cohort, 8 assigned to AL-335 and 2 assigned to placebo). Based on the emerging data, an additional cohort of 10 subjects with CHC genotype 1 infection may be enrolled to evaluate an alternative dose of AL-335.

The following cohorts may be enrolled after a review of the safety and efficacy of the initial MAD cohorts which will be conducted by the sponsor in consultation with the principal investigators. The dose to be administered will have demonstrated at least a mean 3 log10 reduction in HCV RNA concentrations in a prior cohort of genotype 1 subjects in combination with an acceptable safety and PK profile.

- Genotype 2: a cohort of ten (10) treatment naïve subjects with genotype 2 CHC infection will be enrolled (8 assigned to AL-335 and 2 assigned to placebo) to evaluate AL-335 dosed once daily for 7 days.
- Genotype 3: a cohort of ten (10) treatment naïve subjects with genotype 3 CHC infection will be enrolled (8 assigned to AL-335 and 2 assigned to placebo) to evaluate AL-335 dosed once daily for 7 days.

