- Genotypes 4-6: a cohort of ten (10) treatment naïve subjects with genotypes 4-6 CHC infection will be enrolled (8 assigned to AL-335 and 2 assigned to placebo) to evaluate AL-335 dosed once daily for 7 days.
- Compensated cirrhosis: a cohort of ten (10) subjects with CHC genotype 1 infection and documented compensated cirrhosis (Child-Pugh Class A) will be enrolled (8 assigned to AL-335 and 2 assigned to placebo) to evaluate AL-335 dosed once daily for 7 days. Sequence analysis of HCV NS5b from CHC GT1 cohorts assigned to receive either AL-335 or placebo will be completed prior to enrollment of subjects with compensated cirrhosis and CHC GT1.

In Parts 1–2, the doses to be evaluated may be modified based on emerging PK and safety data. However, there will be no more than a three-fold increase in dose per cohort (see *Cohort Progression Guidelines*, Section 5.1.1) and the mean exposure for ALS-022227 (AUC0-24) at a dose level will be projected not to exceed 75,500 ng·h/mL.

In Part 3, the doses to be evaluated may be modified based on emerging PK, HCV RNA and

safety data. However, the maximum dose administered will not exceed the maximum tolerated dose observed in Part 1; the mean exposure for ALS-022227 ( $AUC_{0-24}$ ) at a dose level will be projected not to exceed 75,500 ng·h/mL; and there will be no more than a three-fold increase in dose per cohort (see *Cohort Progression Guidelines*, Section 5.1.1).

In Parts 1–3, an increase in dose will only occur if the previous dose is demonstrated to be generally safe and tolerable (see *Cohort Progression Guidelines*, Section 5.1.1). Before the second and subsequent cohorts are conducted, safety data from the prior cohort will be reviewed by the Principal Investigator (PI) and Sponsor.

Part 3 will commence when the third dose of Part 1 is found to be safe and tolerable based upon a review of the blinded safety data by the PI and the Sponsor. Dosing will take place after a standard meal.

Safety and tolerability will be evaluated on an ongoing basis through assessment of adverse events, blood and urine sample analyses, collection of electrocardiograms (ECG), vital signs and physical examinations. In the event a safety signal is detected, the pharmacokinetic/pharmacodynamic (PK/PD) relationship between AL-335 and its metabolites and various safety parameters including ECG changes, vital signs, and relevant laboratory parameters will be evaluated.

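### In Part 3 Cohorts 5–8 a met toxicity trigger requires no pause and no comprehensive review when no dose increase is pending, and in no cohort does a trigger pause enrolment at the current dose

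*Protocol*

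**What the plan says.** Protocol Section 5.1.1 introduces its triggers with "Dose escalation will be suspended". There are five, each counted within a dose cohort:

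- four or more subjects with related moderate events;
- two or more with related severe events;
- one or more with a related life-threatening event;
- three or more with sustained QTcF above 500 msec and a rise above 60 msec;
- three or more with a sustained resting heart rate above 100.

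Section 10.0 uses the term dose cohort for each 10-subject group in Part 3.

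Two further actions are described. After a life-threatening event the sponsor's "Medical Monitor will review the treatment allocation to determine if the subject is receiving study medication or placebo", and escalation may restart if it was placebo. Then: "If dose escalation is suspended, a more comprehensive review of the safety data will be undertaken by the Sponsor and the PI". The possible outcomes of that review are to "continue with dose escalation, repeat a previously evaluated dose, evaluate a lower dose, modify the protocol, or terminate the study".

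For Part 3 Cohorts 5–8, Section 2.1 requires a dose that has already produced a mean reduction of at least 3 log10 "in HCV RNA concentrations in a prior cohort of genotype 1 subjects in combination with an acceptable safety and PK profile". Table 5.1-1 lets the Sponsor set that dose once the initial genotype 1 cohorts are complete, no earlier than Cohort 2. Section 5.1.1 also says: "Additional subjects may be recruited to evaluate a dose further if the data obtained from the initial cohort is not sufficiently robust".

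**The concern.** The thresholds are counted in every cohort, but their consequence is written for escalation steps only. A cohort that repeats a tested dose in a new population is not an escalation step. If no higher dose is waiting elsewhere in Part 3, there is nothing to suspend, so the condition that starts the comprehensive review is never met.

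These are the cohorts that bring in new populations, including the only subjects with cirrhosis, whom Section 1.2 describes as having more advanced liver disease. With no increase pending, two related severe events early in such a cohort would oblige nobody to stop enrolling at that dose or to begin the comprehensive review. After one related life-threatening event the only trigger-specific duty would be the allocation check, and the protocol uses that check only to decide whether escalation may restart.

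**Working it through.** The protocol states no figure to reproduce here, so the check traces what a met trigger requires and then counts who is affected.

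**1. Effect of a met trigger, by situation (Section 5.1.1)**

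| Where the trigger is met | Escalation suspended? | Comprehensive review required? | Enrolment at that dose paused? |
|---|---|---|---|
| Genotype 1 cohort with a higher dose to follow | Yes | Yes | No |
| Cohorts 5–8, a higher dose pending in Part 3 | Yes | Yes | No |
| Cohorts 5–8, no higher dose pending | Nothing to suspend | No | No |
| Added subjects at an existing dose, no higher dose pending | Nothing to suspend | No | No |

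**2. When an increase could still be pending.** Cohorts 5–8 may start after Cohort 2, so Cohort 3 (800 mg) may be outstanding. Optional Cohort 4 may go up, but Section 5.1.1 also allows a lower dose, in which case it is not an escalation either. The Sponsor sets the dose for each of Cohorts 5–8, so a later one could be higher than an earlier one. Cohort 8 must wait for NS5b sequencing of the genotype 1 cohorts. If that means all of them, no genotype 1 escalation is open when it enrols, although a later cohort at a higher dose still could be.

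**3. Subjects in the third row.** Between 0 and 4 cohorts of 10 (8 AL-335, 2 placebo):

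- subjects: 0 to 4 × 10 = 40;
- on AL-335: 0 to 4 × 8 = 32;
- share at the maximum: 40/70 = 57% of the planned CHC subjects, or 40/80 = 50% if Cohort 4 is used.

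**4. Other safeguards**

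- Section 2.1: "Before the second and subsequent cohorts are conducted, safety data from the prior cohort will be reviewed". Section 5.1.1 makes the Part 3 decision to proceed "based on a blinded review of clinical safety data through Day 9". Both control opening of the next cohort. Dosing ends on Day 7, so a Day 9 review comes after the current cohort's last dose if its subjects start together, and the last cohort has no successor.
- Section 7.2.6 (SAE notification within 24 hours) and Section 7.4 (ongoing sponsor AE review) are mandatory, but set no count and no hold.
- Section 4.5 (individual withdrawal) and Section 4.6 (termination) are discretionary.

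**5. Doses still scheduled after one life-threatening event.** Assume all 10 subjects start on the same day, and the affected subject is on AL-335 and withdrawn after dose d. The others then have 9 × (7 − d) doses left, of which 7 × (7 − d) are AL-335:

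- d = 1: 9 × 6 = 54 (7 × 6 = 42 AL-335)
- d = 2: 9 × 5 = 45 (7 × 5 = 35)
- d = 6: 9 × 1 = 9 (7 × 1 = 7)

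The protocol does not fix a same-day start, and there may be up to six sites. With staggered starts the range is 0 (the others have finished) to 9 × 7 = 63 (7 × 7 = 49 AL-335; none of the others has started).

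**6. How often a threshold might be met (illustration only).** With 8 subjects on AL-335, placebo ignored and an assumed related severe-event rate p, P(at least 2) = 1 − (1 − p)^8 − 8p(1 − p)^7. This is 0.06, 0.19, 0.50 and 0.74 for p = 5%, 10%, 20% and 30%. These rates are assumptions, not protocol figures.

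**The case against.** The strongest reply is that Cohorts 5–8 are well supervised without the triggers. Sponsor and PI must review safety before each later cohort, and 8 of 10 subjects must complete dosing first. If the cohorts run one after another, a trigger in Cohort 5 is seen before Cohort 6 opens. Subjects stay in the clinic from Day −2 to Day 9, with daily liver tests and ECGs on Days 1–8. The investigator may withdraw anyone, Section 4.6 names AE incidence or severity as a ground for termination, and the dose has already shown an acceptable profile in genotype 1. On this view the absence of an automatic hold in a seven-day inpatient cohort is a design choice.

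Much of this stands, and it rules out stronger readings that a reader might infer:

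- That triggers never block enrolment. Suspension does block the next higher-dose cohort; the gap concerns the current cohort and further subjects at the same dose.
- That all of Cohorts 5–8 lack the review. Any pending increase, including a later cohort at a higher dose, restores it.
- That subjects are left unprotected or that a signal would be ignored. The documents support neither.
- That every serious trigger needs an automatic dosing hold. For the severe-event and QTcF counts that is largely preference.

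The reply does not answer the central point. The protocol sets numerical thresholds for these cohorts and, in an ordering it permits, gives them no general effect. Review before the next cohort does not protect the current or the last one.

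**Conclusion.** The point holds and should be fixed. On the text, a trigger met in Cohorts 5–8 with no dose increase pending in Part 3 requires no pause and no comprehensive review; the allocation check after a life-threatening event is the one trigger-specific action left. Separately, no trigger in any cohort itself pauses enrolment into that cohort or of added subjects at the same dose.

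The size is conditional. The missing review may affect nobody or all of Cohorts 5–8, according to cohort order. The cirrhosis cohort is the likeliest to be affected, if the sequencing requirement covers every genotype 1 cohort and no later cohort goes higher. The dose counts show how many administrations a hold would cover under the stated assumptions, including that nobody intervenes; they do not measure risk.

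**What to change.** Amend Section 5.1.1 as follows, leaving thresholds and reviewers unchanged.

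1. State that the triggers apply to every cohort, including Part 3 Cohorts 4–8 and additional subjects at an existing dose.
2. State that any met trigger suspends both escalation and new enrolment at that dose.
3. In "If dose escalation is suspended, a more comprehensive review of the safety data will be undertaken by the Sponsor and the PI", replace the opening condition with: if any trigger is met.
4. Add resuming or stopping enrolment and dosing in the affected cohort to the listed review outcomes.
5. After a related life-threatening event, also hold the remaining doses in that cohort until the allocation check. Release the hold if the subject was on placebo; otherwise keep it until the review is done.

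Leave dosing holds after the severe-event and QTcF triggers to the review.

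The cost is amendment wording, a short enrolment pause in a triggered cohort and, after a life-threatening event, possibly some incomplete seven-day courses with loss of those subjects' Day 7 PK, viral-kinetic and resistance data. Confining the automatic dosing hold to one trigger, with release on a placebo result, keeps that loss small.

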### **7.2.2 Documenting and Reporting Adverse Events**

**Record all AEs** that occur from Day 1 (from start of study medication administration) to the follow-up visit, regardless of the intensity, seriousness, or relationship to study drug, on the AE CRF, for all enrolled subject. Subjects who do not enroll (i.e., screen failures), collect AEs until the time of screen failure.

Grade AEs (serious and nonserious) in accordance with the scale presented below:

- Mild adverse event (minor; no specific medical intervention; asymptomatic laboratory findings only;; marginal clinical relevance); does not interfere with regular activities

- Moderate adverse event (minimal intervention; local intervention; noninvasive intervention [packing, cautery]); moderate level of discomfort and significantly interferes with regular activities
- Severe and undesirable adverse event (significant symptoms requiring hospitalization or invasive intervention; transfusion; elective interventional radiological procedure; therapeutic endoscopy or operation); significant level of discomfort and prevents regular activities
- Life-threatening or disabling adverse event (complicated by acute, life-threatening metabolic or cardiovascular complications such as circulatory failure, hemorrhage, sepsis. Life-threatening physiologic consequences; need for intensive care or emergent invasive procedure; emergent interventional radiological procedure, therapeutic endoscopy or operation).

Once an event has resolved, any recurrence will be reported as a new event with a corresponding grade.

Whenever possible, report AEs as a specific diagnosis or syndrome (e.g., flu syndrome) rather than as individual signs or symptoms. If no specific diagnosis or syndrome is identified, AEs should be reported as separate and individual events.

An AE includes the following:

- Pre-existing event that increases in frequency or intensity.
- Condition detected or diagnosed during the study period, even though it may have been present, in retrospect, prior to the first dose of study drug.
- Laboratory abnormalities outside of normal limits and requiring therapeutic intervention.
- An overdose of the study drug without any signs or symptoms will be considered an AE. A calculated dose that exceeds its correct dose by 10% or more and is administered to the subject will be considered an overdose and documented as an AE.

The following events **will not** be identified as AEs in this study:

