*Grading Adult and Pediatric AEs*

The DAIDS grading table includes parameters for grading both adult and pediatric AEs. When a single set of parameters is not appropriate for grading specific types of AEs for both adult and pediatric populations, separate sets of parameters for adult and/or pediatric populations (with specified respective age ranges) are provided. If there is no distinction in the table between adult and pediatric values for a type of AE, then the single set of parameters listed is to be used for grading the severity of both adult and pediatric events of that type.

*Determining Severity Grade*

If the severity of an AE could fall under either one of 2 grades (e.g., the severity of an AE could be either grade 2 or grade 3), select the higher of the 2 grades for the AE.

**Note:** The laboratory normal ranges should be taken into consideration to assign gradings to a laboratory value.

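### Section 5.1.1: the moderate-AE suspension trigger leaves out worse grades, so three moderate subjects plus one severe-only subject force no suspension, while four moderate subjects do

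*Protocol*

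**What the plan says.** Protocol section 5.1.1 lists five suspension triggers joined by OR. Three concern adverse events judged related to study drug:

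- "If 4 or more subjects in a dose cohort experience moderate AEs or toxicities";
- "If 2 or more subjects in a dose cohort experience severe AEs or toxicities";
- one or more subjects with a life-threatening event, where escalation may resume if that subject proves to have been on placebo.

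The other two (QTcF and resting heart rate, three or more subjects each) do not bear on this point. Once escalation is suspended, "a more comprehensive review of the safety data will be undertaken by the Sponsor and the PI", and that review may decide to continue.

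Section 7.2.2 defines the grades as separate categories: "Moderate adverse event (minimal intervention; local intervention; noninvasive intervention" and so on for moderate, and "Severe and undesirable adverse event (significant symptoms requiring hospitalization or invasive intervention" and so on for severe. Section 7.2 also applies the grading table in Appendix E. Its general instructions say that, for an event that could fall in either of two grades, the investigator should "select the higher of the 2 grades for the AE".

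Outside the triggers, section 2.1 states that "an increase in dose will only occur if the previous dose is demonstrated to be generally safe and tolerable". Section 5.1.1 makes each Part 3 progression decision "based on a blinded review of clinical safety data through Day 9".

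**The concern.** A suspension rule should never become easier to pass as toxicity gets worse. Here the first trigger names one grade and has no upward extension, and nothing in the list adds moderate and severe subjects together. An event graded severe is not also recorded as moderate, so a subject whose only related event is severe contributes nothing to the count of four.

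At stake are the mandatory suspension and the fuller safety review that follows it. Single doses up to 1200 mg have already been given (section 1.1), so the rule now matters mainly for the seven-day steps from 400 to 600 to 800 mg in Part 3 and for any optional higher-dose cohort.

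**Working it through.** **Logic.** Let m be the number of subjects whose related events are moderate at worst, s the number with a severe related event, and l the number with a life-threatening one. Assume at first that no severe subject also had a separate moderate related event.

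- As written: suspend if m ≥ 4, or s ≥ 2, or l ≥ 1.
- With worse grades counted in the first trigger: suspend if m + s + l ≥ 4, or s ≥ 2, or l ≥ 1.

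The rules can differ only where the written rule is silent, so m ≤ 3, s ≤ 1 and l = 0. Within that region m + s reaches 4 only at m = 3, s = 1. Enumerating all splits for 6, 8 and 10 subjects gives the same single case.

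| Pattern | m ≥ 4? | s ≥ 2? | Suspension forced as written |
|---|---|---|---|
| 4 moderate, 0 severe | yes | no | yes |
| 3 moderate, 1 severe | no (3) | no (1) | no |
| 2 moderate, 2 severe | no (2) | yes | yes |

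**Frequency.** The visible text gives no related-event rates by grade, so the rates below are assumptions. With n subjects at risk, moderate-only rate p and severe rate r:

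P(3,1) = n! / (3! · 1! · (n−4)!) × p³ × r × (1 − p − r)^(n−4)

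The multiplier is 60 for n = 6, 280 for n = 8 and 840 for n = 10. These stand for the active subjects in a Part 1 cohort, the active subjects in a Part 3 cohort, and all Part 3 subjects if placebo subjects had the same rates. For n = 8, p = 0.40, r = 0.10: 280 × 0.064 × 0.10 × 0.5⁴ = 0.112.

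| Moderate-only / severe | n = 6 | n = 8 | n = 10 |
|---|---|---|---|
| 10% / 2% | 0.1% | 0.3% | 0.8% |
| 20% / 5% | 1.4% | 3.5% | 6.0% |
| 30% / 5% | 3.4% | 6.8% | 8.6% |
| 40% / 10% | 9.6% | 11.2% | 8.4% |

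These are maxima. A severe subject who also had a separate moderate related event still counts in the first trigger. If a share q of severe subjects did, each figure is multiplied by (1 − q). With q = 50% and n = 8 the column becomes 0.2%, 1.8%, 3.4% and 5.6%.

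**Against overall suspension.** For n = 8 at 40%/10%, the written rule does not suspend when m ≤ 3 and s ≤ 1:

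- s = 0: 0.0039 + 0.025 + 0.070 + 0.112 = 0.2109
- s = 1: 8 × 0.10 × (0.0078 + 0.04375 + 0.105 + 0.140) = 0.2373

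Suspension as written is 1 − 0.4482 = 55.2%. Counting worse grades adds P(3,1) = 11.2 points, giving 66.4%. The other three rate pairs, in table order, go from 1.5% to 1.9%, 11.2% to 14.8%, and 24.7% to 31.4%.

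**The case against.** The best reply is that the triggers form a ladder, 4 then 2 then 1, and that anyone applying it would count a severe case on the moderate rung. Strict literalism also fails elsewhere in the same bullets. They count events possibly or probably related, while the attribution scale in section 7.2.3 runs Related, Possibly Related, Unlikely Related and Not Related, and nobody would leave out a plainly related event.

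The consequence is small too. The Sponsor and the investigator must review the prior cohort before any increase, and they would see these four subjects. Suspension hands the decision to the same parties, who may continue. Dose is separately limited by the maximum tolerated dose in Part 1, the exposure limit and the three-fold rule. The upper frequencies have no support in the protocol, which reports no serious adverse events in 40 volunteers given single doses or two 400 mg doses.

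Much of this stands. A purposive reader would see no gap, the safeguards are real, and the frequencies only illustrate. But the text does not contain the purposive reading, and a safety trigger used at up to six sites in four countries should not depend on each reader supplying it. The numerical triggers were placed on top of the routine review, and they alone force suspension; that layer fails for this pattern. Single-dose data in healthy volunteers do not settle rates under seven-day dosing in patients.

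**Conclusion.** The point holds as a minor defect in a stated safety rule. Read literally, three moderate subjects plus one severe-only subject do not force suspension, while four moderate subjects do. That conclusion follows from the wording alone and needs no assumed rates.

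Its size does depend on assumptions. Across the rates and cohort sizes tried, the pattern arises in at most about 0.1% to 11% of cohorts, and in fewer if severe subjects also tend to have moderate related events. The top of that range requires rates at which the existing rule already suspends 55% of cohorts. What is lost is the mandatory suspension and the fuller review, not all control over escalation.

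**What to change.** Change the first trigger only, so that it counts four or more subjects with *moderate or worse* related events. Keep the thresholds of 4, 2 and 1 and leave the other triggers as they are.

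The cost is two words and an occasional extra pause, in at most the same 0.1% to 11% of cohorts under the assumed rates. Section 5.1.1 still allows escalation to continue after the review.

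There is one side effect. Where a single life-threatening case turns out to be on placebo, that subject would still count towards the four. Three moderate subjects, or two moderate plus one severe, alongside that case would then stay suspended despite the placebo release. If the sponsor wants the release untouched, *moderate or severe* closes the same gap without this effect: it holds the cohort only when the three moderate plus one severe pattern is itself present.
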